### 11.3 Subject Data

In all enrolled subjects, frequency tabulation will be performed for randomized subjects, subjects who received the study drug, subjects who did not receive the study drug, subjects who completed the study, and subjects who have withdrawn from the study and reasons for withdrawal. In randomized subjects, frequency tabulation will also be made for inclusion/exclusion in/from each analysis set, and reasons for exclusion. Baseline characteristics will be tabulated for subjects included in the safety analysis set, solicited safety analysis set, FAS, PPS, FAS for Immunogenicity, PPS Immunogenicity, Immunized FAS, Immunized PPS, Immunized FAS for Immunogenicity, and Immunized PPS for Immunogenicity. The use of concomitant medications will also be tabulated for subjects included in the safety analysis set.

### 11.4 Efficacy Analysis

The primary analysis set for immunogenicity endpoints is the Immunized PPS for Immunogenicity or PPS for Immunogenicity, and a supplementary analysis will also be performed in the Immunized FAS for Immunogenicity or FAS for Immunogenicity.

In addition, the primary analysis set for COVID-19 incidence is the Immunized PPS or the PPS, and a supplementary analysis will also be performed in the Immunized FAS or the FAS. The analyses will be performed based on the treatment group to which each subject was assigned.

#### 11.4.1 Primary Efficacy Analysis

The following analyses will be performed for the Immunized PPS for Immunogenicity.

The GMT ratio (DS-5670d group vs. Comirnaty RTU IM group) for blood neutralizing activity against SARS-CoV-2 (Omicron strain XBB.1.5.6) at 4 weeks after study drug administration and its 2-sided 95% confidence interval will be calculated by administration arm. The difference in seroresponse rate (DS-5670d group – Comirnaty RTU IM group) for blood neutralizing activity against SARS-CoV-2 (Omicron strain XBB.1.5.6) at 4 weeks after study drug administration and its 2-sided 95% confidence interval will be calculated.

A linear model will be applied with blood neutralizing activity against SARS-CoV-2 (Omicron strain XBB.1.5.6) at 4 weeks after study drug administration as an explained variable, administration

Confidential

arm as an explanatory variable, and baseline value (common logarithmic value), a history of SARS-CoV-2 infection and vaccination with SARS-CoV-2 vaccine as covariates, based on which the GMT ratio (DS-5670d group vs. Comirnaty RTU IM group) and its 2-sided 95% confidence interval will be calculated. The covariates may be changed depending on subject enrollment.

In addition, the difference in seroresponse rate (DS-5670d group – Comirnaty RTU IM group) for blood neutralizing activity against SARS-CoV-2 (Omicron strain XBB.1.5.6) at 4 weeks after study drug administration and its 2-sided 95% confidence interval will be calculated. This analysis may be changed to stratified analysis depending on subject enrollment.

DS-5670d will be judged to be non-inferior to Comirnaty RTU IM if the lower limit of 2-sided 95% confidence interval in adjusted GMT ratio (DS-5670d group vs. Comirnaty RTU IM group) is greater than 0.67 and simultaneously the lower limit of 2-sided 95% confidence interval of the difference in seroresponse rate (DS-5670d group – Comirnaty RTU IM group) is greater than –10%.

The same supplementary analyses will also be performed for the Immunized FAS for Immunogenicity.

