#### 5.1.2 Method of Treatment Allocation

The independent biostatistician will prepare a subject randomization list showing a correspondence between subject numbers and study drugs (investigational product or comparator).

Subjects will be randomized in a 1:1 ratio to the DS-5670d group or Comirnaty RTU IM group, with study site, age (12 to 17 years, 18 to 64 years, 65 years and older), the presence or absence of a history of SARS-CoV-2 infection (yes, no), the presence or absence of a history of vaccination with SARS-CoV-2 vaccine (yes, no) as stratification factors based on the information entered in the Interactive Response Technology (IRT). The presence or absence of a history of SARS-CoV-2 infection used as a stratification factor will be based on the history of SARS-CoV-2 infection reported by the subject or legal representative at informed consent (self-reported SARS-CoV-2 infection history) and the SARS-CoV-2 antibody test result from the rapid test kit at the time of eligibility evaluation. A subject will be defined as having a history of SARS-CoV-2 infection if he/she is determined to have a self-reported SARS-CoV-2 infection history at informed consent or have a positive SARS-CoV-2 antibody with the rapid test kit at the time of eligibility evaluation. Otherwise, the subject will be defined as having no history of SARS-CoV-2 infection.

The procedures for subject enrollment are shown in [Figure 5.1-1](#).

After obtaining written consent from the subject or subject's legal representative, the investigator or subinvestigator will prepare a subject screening list, and confirm the eligibility of the subject.

The investigator, subinvestigator, or study staff will register the required information in the IRT after obtaining informed consent. The IRT will allocate a study-specific subject number. The investigator, subinvestigator, or study staff will enter confirmation of the subject eligibility in the IRT. The IRT will randomize the eligible subject to an administration and notification of the assigned study drug will be sent to the unblinded personnel at the study site (See Section 5.1.3).

After the unblinded personnel at the study site (study drug manager or study drug management assistant designated by the study drug manager, study drug preparer, and study drug administration personnel) will confirm the assigned study drug based on the IRT notification, the assigned study

Confidential

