Multiplicity of the test associated with multiple non-inferiority hypotheses in multiple populations (ABC combined and ABCD combined) will be controlled by fixed sequence testing. First, the non-

Confidential

inferiority of the DS-5670 group to the Comirnaty RTU IM group will be tested in the ABC combined population, and only if the non-inferiority is confirmed, the non-inferiority of the DS-5670d group to the Comirnaty RTU IM group will be verified in the ABCD combined population. All hypotheses will be evaluated at a one-sided 2.5% significance level.

With reference to the PMDA notification "Principles for the Evaluation of Vaccines Against the Novel Coronavirus SARS-CoV-2, (Appendix 4) Immunogenicity-based evaluation of variant vaccines modified from parent vaccines and booster vaccines with new active ingredients," the non-inferiority margins for the GMT ratio and the difference in the seroresponse rate are set at 0.67 and -10%, respectively.

In this study, analyses will be performed twice. The first analysis will be the primary analysis of immunogenicity and safety. The primary immunogenicity and safety endpoints will be evaluated to verify the non-inferiority of DS-5670d group to Comirnaty RTU IM group once when immunogenicity and safety data are collected for all subjects for 4 weeks after study drug administration or when the study is terminated. The second analyses will be performed when or the immunogenicity and safety data for 26 weeks after study drug administration have been obtained for all subjects or the study termination.

Unless otherwise specified, continuous variables will be summarized by presenting the number of subjects, arithmetic mean, standard deviation, minimum, median, and maximum, and categorical variables will be summarized by calculating the frequency and proportion. Unless otherwise specified, baseline values from each subject will be the last observed values that are available before study drug administration. Changes from baseline (eg, change, shift table) will be analyzed in subjects whose baseline values and at least one post-treatment value are available. An outline of the statistical analyses is provided below. Statistical methods will be specified in more details in separately prepared Statistical Analysis Plan (SAP).

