## 11.4.3 Exploratory Efficacy Analysis

Subgroup analyses will be performed for immunogenicity (eg, GMT of blood neutralizing activity against SARS-CoV-2 [Omicron strain XBB.1.5.6], seroresponse rate, etc.) according to baseline characteristics (eg, sex, history of SARS-CoV-2 infection, vaccination with SARS-CoV-2 vaccine).

The GMTs of blood neutralizing activity against SARS-CoV-2 (Omicron strain XBB.1.5.6) at 8 weeks, 12 weeks, 16 weeks, 20 weeks, and 26 weeks after study drug administration and their 2-sided 95% confidence intervals and the seroresponse rates will be calculated.

The GMTs of blood neutralizing activity against SARS-CoV-2\* at 4 weeks, 8 weeks, 12 weeks, 16 weeks, 20 weeks, and 26 weeks after study drug administration and their 2-sided 95% confidence intervals, and the seroresponse rates will be calculated.

\*: Details of variants to be evaluated are specified in a separately prepared plan.

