#### Power for the primary objective

With the sample size of 690 subjects in the population with at least either a history of SARS-CoV-2 infection or vaccination with SARS-CoV-2 vaccine (ABC combined) and an assignment ratio (DS-5670d group : Comirnaty RTU IM group) of 1:1, and assuming that the percentage of enrolled subjects who do not contribute to immunogenicity evaluation due to reasons such as exclusion from analysis set and subjects' withdrawal from the study is 10.0%, the GMT ratio (DS-5670d group vs. Comirnaty RTU IM group) for blood neutralizing activity against SARS-CoV-2 at 4 weeks after study drug administration is 1.0, and the common standard deviation of neutralizing activity (common

Confidential

logarithmic value) is 0.533, the statistical power to detect the non-inferiority for GMT would be 98.2% at 1-sided significance level of 0.025. The standard deviation was determined based on the results of Study DS5670-103 and Study DS5670-146 to compare DS-5670a and Comirnaty IM (monovalent: original strain) in subjects aged 18 years and older.

On the other hand, assuming that the seroresponse rate for blood neutralizing activity against SARS-CoV-2 at 4 weeks after study drug administration is 80.0% in both the DS-5670d group and Comirnaty RTU IM group, the statistical power to detect the non-inferiority for seroresponse rate would be 87.2% at 1-sided significance level of 0.025.

Therefore, the power for the non-inferiority which simultaneously satisfies these primary endpoints is 85.6% ( $= 98.2\% \times 87.2\%$ ) assuming that the non-inferiority in terms of GMT and seroresponse rate are respectively independent.

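### Age is a randomisation stratum but is missing from the primary GMT model, and the lower-powered co-primary, seroresponse, is crude unless an undefined enrolment condition makes it stratified

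*Protocol*

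**What the plan says.** Protocol 5.1.2 randomises 1:1 with four stratification factors: study site, "age (12 to 17 years, 18 to 64 years, 65 years and older"), infection history (yes/no) and vaccination history (yes/no).

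Protocol 11.4.1 defines the two co-primary analyses in the Immunized PPS for Immunogenicity:

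- **GMT ratio.** A linear model with treatment arm, log10 baseline value, infection history and vaccination history. Age and site are not in it. The paragraph ends: "The covariates may be changed depending on subject enrollment".
- **Seroresponse difference.** A difference in proportions with a two-sided 95% interval and no adjustment. The next sentence reads: "This analysis may be changed to stratified analysis depending on subject enrollment".

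Non-inferiority requires both lower limits to clear their margins. Section 11.4.2.1 applies the same analysis to the key secondary population, so both conditional sentences carry over to it. Section 11.6 gives the power as 98.2% for GMT, 87.2% for seroresponse and 85.6% jointly. Section 11.7 says that the SAP will be final before unblinding.

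**The concern.** When randomisation is balanced within strata that predict the outcome, the arm difference varies less than a crude interval supposes. An analysis that ignores those strata keeps its type I error but has intervals that are wider than needed.

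Here the adjustment goes to the endpoint that needs it least. GMT, with 98.2% power, is adjusted for baseline and both histories. Seroresponse, with 87.2%, largely determines the joint power and by default is adjusted for nothing. Age was judged important enough to stratify on, yet it enters neither analysis and no reason is given.

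The two conditional sentences do permit age to be added and seroresponse to be stratified. But they name no criterion, no cell-size threshold and no fallback model, and 11.4.6 marks blind review as not applicable. A reader of the protocol therefore cannot tell which confirmatory analysis will decide the trial.

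**Working it through.** **Inputs from the documents**

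- Level (11.1): "All hypotheses will be evaluated at a one-sided 2.5% significance level".
- Margins (11.1): "the non-inferiority margins for the GMT ratio and the difference in the seroresponse rate are set at 0.67 and -10%, respectively"; −log10(0.67) = 0.1739.
- Size (11.6): "With the sample size of 690 subjects in the population with at least either a history" of infection or vaccination, so 345 per arm. The assumed non-evaluable share ("withdrawal from the study is 10.0" percent) leaves 345 × 0.9 = 310.5, taken as n = 310 per arm.
- SD of log10 titre 0.533; true GMT ratio 1.0; seroresponse 80.0% in both arms (11.6).

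**Step 1: reproduce the stated power**

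- GMT: SE = 0.533 × √(2/310) = 0.0428. Power = Φ(0.1739/0.0428 − 1.96) = 98.2%, as stated.
- Seroresponse, unpooled Wald: SE = √(2 × 0.16/310) = 0.03213. Power = Φ(0.10/0.03213 − 1.96) = 87.5%.
- Seroresponse, Farrington–Manning: the rates restricted to a 10-point difference are 0.841 and 0.741, giving a null SE of 0.03241. Power = Φ((0.10 − 1.96 × 0.03241)/0.03213) = 87.2%, as stated. At 355 per arm the same formula gives the 91.2% stated for the key secondary analysis.
- Joint: 98.2% × 87.2% = 85.6%, as stated.

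The planning figures therefore use the unadjusted SD and crude proportions. They do not rely on any adjustment.

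**Step 2: seroresponse stratified by age band (assumed rates)**

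The documents give no rates by stratum, so these are assumptions. Replace 0.16 by the within-stratum variance v = Σ wᵢpᵢ(1 − pᵢ), with the overall rate held at 80%. Power = Φ(0.10/√(2v/310) − 1.96), to be compared with 87.5% on the same Wald scale. Age shares tried: 10/60/30%, 15/60/25% and equal thirds.

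| Rates differ per band by | v | Power |
|---|---|---|
| 5 points | 0.1583 to 0.1591 | 87.7 to 87.9% |
| 10 points | 0.1533 to 0.1564 | 88.3 to 88.9% |
| 15 points | 0.1450 to 0.1519 | 89.1 to 90.5% |

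One case by hand, equal thirds with rates 90/80/70%: v = (0.09 + 0.16 + 0.21)/3 = 0.1533, SE = 0.03145, power = Φ(3.179 − 1.96) = 88.9%.

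**Step 3: seroresponse with any set of strata, including the two histories (assumed variance reduction)**

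| Variance reduction | Stratified power | Joint with GMT |
|---|---|---|
| 0% | 87.5% | 86.0% |
| 2% | 88.2% | 86.6% |
| 5% | 89.1% | 87.5% |
| 10% | 90.7% | 89.1% |

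Steps 2 and 3 together put the gain over 87.5% at roughly 0.2 to 3 points.

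Part of that gain reaches the crude analysis anyway, because stratified randomisation steadies the estimate even when the interval ignores it. Taking power as Φ((0.10 − 1.96 × 0.03213)/√(2v/310)), the crude analysis would have 87.8%, 88.1% and 88.8% under reductions of 2%, 5% and 10%. The part that depends on the choice of analysis is then 0.4, 1.0 and 1.9 points.

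**Step 4: age added to the GMT model (assumed residual R²)**

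With the SD multiplied by √(1 − R²), R² of 2%, 5% and 10% gives 98.4%, 98.6% and 99.0% against 98.2%: a gain of 0.2 to 0.8 points.

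**The case against.** The strongest reply is that the trial is powered for the analysis as written. The stated figures reproduce without adjustment, and an interval that ignores strata errs on the conservative side, which is the safe side in a non-inferiority trial. That stands: a reader might infer a shortfall against 85.6%, and there is none.

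The second reply is that the latitude is bounded. The trigger is enrolment, not outcome by arm; 11.7 fixes the SAP before unblinding; and the conditional sentences allow exactly the analysis asked for here. This also stands against any inference that the model could be chosen after seeing results by arm. It does not remove the omission of age from the protocol's model, or the crude default for seroresponse.

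Other stronger readings that the documents do not support:

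- **A large power gain.** Positing very different response rates between prior-immunity groups produces one, but the protocol gives no such rates, and of the three group shares only the 14.5% target for infected, unvaccinated subjects.
- **A model on raw titres.** Section 11.4.1 attaches the log scale to the baseline value only. But a GMT ratio requires logs, and 11.6 gives the SD in log10 units, so the intention is clear and the sentence is merely loose.
- **Age left out of the subgroups.** The list in 11.4.3 is one of examples ("eg, sex, history of SARS-CoV-2 infection, vaccination with SARS-CoV-2 vaccine"), so it does not exclude age.

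Sparse cells are a fair practical objection. Three age bands by three history groups make nine cells, and the infected, unvaccinated group is planned at only 50 per arm. A pooling rule is therefore a necessary part of the change.

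**Conclusion.** The point holds as forgone precision and an unfixed choice of analysis; the planned power and the error control are sound. The factual part rests on the text alone: age is a stratum and is not in the GMT model, and seroresponse is crude by default with an undefined switch to stratification.

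The size rests on assumptions, since the documents do not say how strongly age or history predicts titre or response. With response rates 5 to 15 points apart per age band, or a 2 to 10% variance reduction from any strata, stratifying seroresponse gains roughly 0.2 to 3 points over the crude planning figure. Adding age to the GMT model gains less than 1 point. The change is worth making because it is nearly free and helps the co-primary that has the least power to spare.

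**What to change.** In Protocol 11.4.1, and in the SAP to match, before unblinding:

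1. Add age band to the GMT model. The two history terms can stay, since they already separate the three groups in the primary population.
2. Make the stratified risk difference, by infection/vaccination history and age band, the primary seroresponse analysis. State in advance the minimum cell size and the order in which sparse cells are pooled.
3. Give the reason for omitting site.
4. Replace both conditional sentences with this fixed analysis and pooling rule.
5. Say which infection-history definition the strata use: 5.1.2 relies on the rapid kit, 11.1 on the central laboratory.
6. As a wording clarification only, state that the modelled outcome is the log10 Day 29 titre.

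The cost is a few sentences and the pooling rule. It needs no new data and no more subjects, and the sample size statement can stay as it is.

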##### 7.1.1.1 Definition of Seroresponse Rate

Percentage of subjects with an increase of  $\geq 4$  times in the blood neutralizing activity against SARS-CoV-2 after study drug administration, compared with the blood neutralizing activity against SARS-CoV-2 before study drug administration.

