## 11.2 Analysis Sets

Subjects with major GCP violations (violation of informed consent obtainment and significant violations of study procedures) will be excluded from all analysis sets.

- All subjects enrolled in the study must have signed the informed consent form by the subjects or legal representatives.
- All randomized subjects must have signed the informed consent form by the subjects or legal representatives.
- The safety analysis set will consist of all subjects who have signed the informed consent form by the subjects or legal representatives and received at least one dose of study drug.
- The solicited safety analysis set will consist of all subjects with at least one available data on presence or absence of occurrence of solicited AE in the safety analysis set.

Confidential

- The full analysis set (FAS) will consist of randomized subjects who meet the following criterion:
  - 1) Having received at least one dose of the study drug.
- The per-protocol set (PPS) will consist of subjects included in the FAS who meet all of the following criteria:
  - 1) Having no significant protocol violations that may affect the efficacy evaluation (eg, violation of inclusion/exclusion criteria, prohibited concomitant medications/therapies, violation of withdrawal/discontinuation criteria).
- The FAS for immunogenicity evaluation (FAS for Immunogenicity) will consist of subjects included in the FAS who meet the following criterion:
  - 1) Having immunogenicity measurements before study drug administration and at least one immunogenicity measurement after study drug administration.
- The PPS for immunogenicity evaluation (PPS for Immunogenicity) will consist of subjects included in the FAS for Immunogenicity who meet the following criterion:
  - 1) Having no significant protocol violations that may affect the immunogenicity evaluation (eg, violation of inclusion/exclusion criteria, prohibited concomitant medications/therapies, violation of withdrawal/discontinuation criteria).
- The FAS with basic immunity (Immunized FAS) will consist of subjects included in the FAS who meet the following criterion:
  - 1) Having at least either a history of SARS-CoV-2 infection\* or vaccination with SARS-CoV-2 vaccine and completed the study drug administration as specified in the protocol.

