## 11.4.2 Secondary Efficacy Analysis

### 11.4.2.1 Key Secondary Efficacy Analysis

The same analysis as the primary efficacy analysis will be performed for the PPS for Immunogenicity. The same supplementary analyses will also be performed for the FAS for Immunogenicity.

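### The seroresponse co-primary, which limits joint power, is compared between arms without adjusting for pre-dose titre; this is an avoidable loss of efficiency, not an error

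*Protocol*

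**What the plan says.** **The two co-primary analyses.** Both conditions must be met for non-inferiority. In section 11.4.1 the GMT ratio comes from a linear model whose covariates include the "baseline value (common logarithmic value") together with infection history and vaccination history, and the decision rule uses that adjusted ratio. The seroresponse difference has no covariates. The text gives the difference in rates "and its 2-sided 95% confidence interval will be calculated. This analysis may be changed to stratified analysis depending on subject enrollment". It names neither the strata nor the condition that would trigger the change.

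**The endpoint.** Section 7.1.1.1 defines seroresponse as at least a 4-fold rise "compared with the blood neutralizing activity against SARS-CoV-2 before study drug administration".

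**Availability of the baseline.** Section 11.2 sets this condition for the FAS for Immunogenicity, and repeats it for the Immunized FAS for Immunogenicity: "Having immunogenicity measurements before study drug administration and at least one immunogenicity measurement after study drug administration". The primary analysis set is a subset of the latter, so the pre-dose titre is complete in it.

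**Power and carry-over.** Section 11.6 states that "the statistical power to detect the non-inferiority for seroresponse rate would be 87.2"%, against 98.2% for GMT and 85.6% jointly. Section 11.4.2.1 carries the method into the key secondary test: "The same analysis as the primary efficacy analysis will be performed for the PPS for Immunogenicity".

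**The concern.** The pre-dose titre is the denominator of the 4-fold rise, so some association with response is expected: a subject who starts high generally has further to climb. The primary population pools people with prior infection, prior vaccination or both. The eligibility criteria set only a minimum of 3 months since the last infection or vaccine dose, so starting titres could vary widely.

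The plan adjusts for this measurement where power is ample (type II error 1.8% for GMT) and leaves it out where power is limiting (12.8% for seroresponse). If baseline predicts response, the seroresponse interval is wider than it need be. The seroresponse difference is also not corrected for chance imbalance in baseline titre, whereas the GMT ratio is. At stake is a few points of power on the condition most likely to decide the primary result, and likewise in the key secondary test.

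**Working it through.** **Inputs from the protocol.** 690 enrolled, 1:1, 10% non-evaluable: 345 × 0.9 = 310.5 per arm. Seroresponse 80% in both arms. GMT ratio 1.0 with log10 SD 0.533. One-sided 2.5%. On the margins: "the non-inferiority margins for the GMT ratio and the difference in the seroresponse rate are set at 0.67 and -10%, respectively".

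**Step 1: reproduce the stated power.**
- GMT: margin on the log10 scale = -log10(0.67) = 0.1739; SE = 0.533 × √(2/310.5) = 0.0428; power = Φ(0.1739/0.0428 − 1.96) = 98.2%. This matches.
- Seroresponse, unpooled normal approximation: SE = √(2 × 0.8 × 0.2/310.5) = 0.0321; power = Φ(0.10/0.0321 − 1.96) = 87.6%.
- Seroresponse, Farrington-Manning (restricted null rates 0.741 and 0.841): null SE = 0.0324; power = Φ((0.10 − 1.96 × 0.0324)/0.0321) = 87.2%. This matches.
- Joint: 0.982 × 0.872 = 85.6%. This matches. The key secondary figures (99.1% and 91.2% with 790 subjects) also reproduce.

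**Step 2: effect of adjusting for baseline.** If baseline titre explains a share R² of the variance of the yes/no response, the variance of the standardised risk difference is multiplied by (1 − R²). Power is then Φ(0.10/(0.0321 × √(1 − R²)) − 1.96).

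**Step 3: plausible values of R².** The protocol gives no baseline SD and no pre/post correlation. The assumed model takes bivariate-normal log10 titres with week-4 SD 0.533, response when the rise is at least log10(4), and an 80% response rate. Then R² = Var[P(response | baseline)]/(0.8 × 0.2), by numerical integration. Gains are measured from 87.6%. Joint power multiplies by 98.2%, starting from 86.1% (0.876 × 0.982, before rounding).

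| Baseline SD (assumed) | Pre/post correlation (assumed) | R² | Seroresponse power | Gain (points) | Joint power |
|---|---|---|---|---|---|
| 0.40 | 0.8 | 0.3% | 87.7% | 0.1 | 86.2% |
| 0.40 | 0.2 | 12.8% | 91.5% | 4.0 | 89.9% |
| 0.533 | 0.8 | 5.1% | 89.2% | 1.6 | 87.6% |
| 0.533 | 0.6 | 10.5% | 90.9% | 3.3 | 89.3% |
| 0.533 | 0.4 | 16.3% | 92.6% | 5.0 | 91.0% |
| 0.533 | 0.2 | 22.6% | 94.3% | 6.7 | 92.7% |
| 0.65 | 0.8 | 18.1% | 93.1% | 5.5 | 91.4% |
| 0.65 | 0.2 | 30.9% | 96.3% | 8.7 | 94.6% |

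In terms of sample size, R² of 10% or 20% means that 690 × 0.9 = 621 or 690 × 0.8 = 552 enrolled would match the power that 690 give unadjusted.

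**Step 4: simulation check** (3000 runs per scenario, 310 per arm, logistic standardisation with an influence-function SE). Unadjusted against adjusted power:
- SD 0.40, correlation 0.4: 87.4% against 89.3%
- SD 0.533, correlation 0.4: 87.8% against 92.8%
- SD 0.533, correlation 0.8: 87.2% against 88.8%

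Over all five scenarios run, which extended to SD 0.7, one-sided error at a true difference of -10 points was 2.3% to 2.8% adjusted and 2.4% to 3.2% unadjusted. Monte Carlo error is about 0.3 points, so adjustment shows no visible inflation.

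**The case against.** **The planned analysis is valid.** Under 1:1 randomisation the unadjusted difference targets the quantity in the hypothesis, and all the stated power figures reproduce. This stands in full. A reader might infer that the seroresponse test is biased or its power overstated; the protocol does not support that.

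**The pre-dose titre is already used.** It enters every subject's response through the 4-fold rule. This also stands. What is missing is its use as a covariate or stratum in the between-arm comparison.

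**The strength of the link is not documented.** A reader might infer that baseline strongly drives response, or that a gain above 7 points can be counted on. The protocol gives no figure for either. A gain of 7.3 points needs R² = 25%, which is not reached at SD 0.533 (5% to 23%). At SD 0.40 with a high correlation the gain almost vanishes. The titre model also assumes normality and does not examine baselines piling up at an assay floor.

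**Randomisation already balances part of the spread.** Stratification by site, age, infection history and vaccination history restrains some baseline imbalance. The figures above take no account of this, so the argument from chance imbalance is weaker than it first looks.

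**The SAP may settle it.** Section 11.1 calls its account an outline, and the reserved stratified analysis could in principle use titre categories. That is possible, but section 11.4.1 writes the unadjusted difference into the decision rule and does not say the strata would involve titre. Strata built from the randomisation factors would not use the measurement.

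**Conclusion.** The point holds as an efficiency improvement whose size depends on assumptions. The plan leaves a complete baseline measurement out of the comparison that limits its joint power, while using it in the comparison that does not. Adjusting would add about 2 to 7 points to seroresponse power if the baseline SD equals the stated 0.533 (joint power about 88% to 93%), about 0 to 4 points at SD 0.40, and about 5 to 9 points at SD 0.65, for pre/post correlations from 0.8 to 0.2. These ranges rest on the assumed spread and correlation and on normal log titres, and they ignore the balance from stratified randomisation. Joint power also assumes, as the protocol does, that the two conditions are independent. Nothing in the stated power or the validity of the planned test needs correcting.

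**What to change.** In section 11.4.1, and through it section 11.4.2.1, pre-specify before unblinding one primary seroresponse analysis:

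- Fit a logistic model with arm, log10 baseline XBB.1.5.6 titre, infection history and vaccination history (the covariates already named for the GMT model).
- Standardise it over the analysis set to the marginal risk difference, with a robust or influence-function 95% confidence interval.
- Keep the -10% margin; it still applies because the target is the same marginal difference.
- Report the unadjusted difference as supplementary.
- Remove the enrolment-dependent switch for this analysis.

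The cost is wording in the protocol and SAP and a few lines of code, with no new data or subjects. The downside is small: the estimate is less simple than a raw difference and relies on a large-sample interval, which is why the unadjusted figure should stand beside it.
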